## Materials and methods

This randomized controlled clinical trial will be conducted at Divino Amor Maternity Hospital (Rio Grande do Norte, Brazil), and patients will be recruited according to the convenience of admission for cesarean birth and distributed into one of the 4 study groups (TENS alone, TENS combined photobiomodulation LLLT, Placebo or Control). This Study, the recruitment started in the July 2023 and not has been completed, the estimate to data collection be completed is august 2025, and results are expected decision-makers in resource allocation for improved care for this population, aiming to obtain insights into the most effective recuperation in postpartum.

To sample calculation, the study sample was the result of a probabilistic sampling process. For each group, the sample number was 17 volunteers, adding 20% of sample losses, the final number for each group was 22 volunteers. Thus, the sample size was 88 participants, based on the degree of pain in the surgical incision region (according to the numeric pain scale [NPS], graded from 0 to 10, and a reduction of 2 points in the pain score) and variable standard deviation for each group of 1.5. The alpha error was 0.05, the test power was 80% [9,13].

Eligibility criteria will encompass women within 8–12 hours post-cesarean birth; only woman habitual risk pregnancy; presence of pain NPS ≥ 3 in the cesarean incision region; no clinical or obstetric complications; no infectious process; undergoing drug treatment (anti-inflammatories, analgesics, and anti-gas drugs) with the same intake interval; absence of neurological or musculoskeletal disorders or alterations; and not physically active.

Exclusion criteria will encompass discontinuation of TENS or the LLLT photobiomodulation interventions; failure to perform the 2-min walk test (2MWT) during the assessment period; presence of clinical or obstetric instability during the assessment period; or patients who have already undergone TENS intervention or have a cognitive deficit.

The sample will be randomized (www.randomization.com) in four groups: TENS intervention combined with LLLT photobiomodulation, TENS alone, placebo, and control. The groups will be coded, and allocation will be done in sealed and opaque envelopes, numbered consecutively.

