**Fig 1 pone.0325254.g001:**
[figure not shown]
Flow chart of study protocol. Flow chart of study protocol. CONSORT 2010 FLOW DIAGRAM.

Our study followed the standard protocol items: recommendations for interventional trials (SPIRIT), which aims to improve clinical trial quality (S1 Checklist, SPIRIT 2013 Checklist) *.

The patients included will be evaluated at three time points: t1 (8–12 h post-cesarean) will use an evaluation form, International Physical Activity Questionnaire (IPAQ) application, pain intensity, pressure pain tolerance and threshold, functional capacity, and cardiorespiratory physiological variables evaluation; t2 (20–24 h post-cesarean) and t3 (44–48 h post-cesarean) will evaluate pain intensity, pressure pain tolerance and threshold, functional capacity, and cardiorespiratory physiological variables.

After t1 and t2, patients allocated to intervention groups will receive their respective protocol.

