### Statistical analysis

Data analysis will be performed using SPSS software version 22.0 (IBM Corp. USA), and in all statistical analyses, p values < 0.05 were considered as statistically significant. Will be performed Shapiro-Wilk test and Levene for normality of the data distribution and equality of variances. Descriptive statistics will be presented using the measures of central tendency. Mauchly’s test of sphericity will be used to validate the correlation of the repeated measures, and if the assumption of sphericity was violated, the Greenhouse-Geisser correction will be applied. Two-way repeated measures ANOVA will be to compare the effects of TENS combined with LLLT photobiomodulation between groups (TENS alone, Placebo and Control) over time (assessment t1, t2 and t3) on a primary outcome (pain) and secondary outcomes (functional capacity, systemic arterial pressure, respiratory and heart rates, oxygen saturation and Functional Independence Measure). When appropriate, post hoc comparisons will be carried out using Tukey’s post hoc correction for multiple comparisons. The effect size will be calculated by Cohen’s. For the missing data, intention to treat analysis will be used.

For better data management and quality control the investigator responsible for randomization will be responsible for organization the collected patients information in spreadsheets and ensure confidentiality without personal identification of the research participants.

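### Intention to treat is named as the missing-data method; as written, with no imputation named, the repeated-measures ANOVA would be a complete-case analysis under an ITT label

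*Protocol article*

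**What the plan says.** The Statistical analysis section of the protocol article fixes four things that bear on this point.

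- Software: "Data analysis will be performed using SPSS software version 22.0".
- Model: "Two-way repeated measures ANOVA will be to compare the effects of TENS combined with LLLT photobiomodulation between groups", "over time (assessment t1, t2 and t3) on a primary outcome (pain" and the secondary outcomes.
- Form of the model: Mauchly's test comes first, and "if the assumption of sphericity was violated, the Greenhouse-Geisser correction will be applied".
- Missing data: "For the missing data, intention to treat analysis will be used". No imputation, likelihood method or other way of keeping a woman with a gap in her data is named.

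Materials and methods starts from 17 women per group and reaches 22 by "adding 20% of sample losses", for 88 in four groups. The same section lists as exclusions stopping the TENS or laser sessions, not completing the two-minute walk test, and clinical or obstetric instability while assessments are under way. The last assessment is at two days: "t3 (44–48 h post-cesarean) will evaluate pain intensity".

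**The concern.** Two different questions are answered with one phrase. Who is analysed, and in which arm, is what intention to treat decides. What to do when a randomised woman has no value at t2 or t3 is a separate matter, and the phrase does not touch it. The protocol does address missing data, but names something that is not a method for it.

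The named model then works against the label. A repeated-measures ANOVA checked by Mauchly's test and corrected by Greenhouse-Geisser is the classical general linear model form. It takes one complete row per woman, and SPSS deletes incomplete rows listwise, outcome by outcome. A woman with t1 and t2 but no t3 disappears from the t2 comparison too.

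The stake is validity. A complete-case ANOVA is in general safe only if the women with gaps are a random subset. The protocol gives reasons to doubt that:

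- Under Cesarean incision pain, movement pain is taken one minute after the walk test, so a woman who cannot walk has no movement-pain value.
- Discontinuing an application can happen only in arms that receive one. Under Intervention protocols, control women receive none.

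**Working it through.** **1. Reproduce the plan's figures.** Inputs from Materials and methods: 17 per group, 20% losses, four groups.

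- 17 / (1 − 0.20) = 21.25, rounded up to 22; 4 × 22 = 88. Both match.
- The starting figure of 17 exceeds the plain two-group figure. With a 2-point difference, SD 1.5 and the stated error rates ("The alpha error was 0.05, the test power was 80" per cent; two-sided assumed), n = 2 × (1.96 + 0.84)² × 1.5² / 2² ≈ 8.8, so 9 per group. The point here does not depend on this.

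**2. Women left under listwise deletion at the plan's allowance.**

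- Per group: 22 × 0.80 = 17.6.
- In total: 88 × 0.80 = 70.4, so about 70 analysed and about 18 randomised women left out.

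**3. Precision lost at t2 by discarding observed values.** Let f be the share of lost women whose t2 value was observed. The standard error with complete cases, relative to using all observed t2 values, is √[(17.6 + 4.4f) / 17.6].

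| Timing of losses | f | Ratio |
|---|---|---|
| All before t2 | 0 | 1.000 |
| Half before t2, half at t3 | 0.5 | √(19.8/17.6) = 1.061 |
| All at t3 | 1 | √(22/17.6) = 1.118 |

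The protocol gives no timing, so the inflation lies between 0 and about 12%.

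**4. Scattered gaps.** If t2 and t3 are each missing independently with probability q (assumed), the share dropped is 1 − (1 − q)².

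| q | Share dropped | Of 88 | Left per group |
|---|---|---|---|
| 5% | 9.75% | about 9 | 19.9 |
| 10% | 19% | about 17 | 17.8 |
| 20% | 36% | about 32 | 14.1 |

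**5. Power.** With 17.6 per group, the expected z is 2 / (1.5 × √(2/17.6)) = 3.955. Unadjusted power is Φ(3.955 − 1.960) = 0.977. With Bonferroni for six pairs it is Φ(3.955 − 2.638) = 0.906. Both exceed 80%.

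**6. Bias, as an illustration.** All of these are assumptions except the SD and the 20%: SD 1.5; equal correlation between assessments; no true difference; 20% lost in one arm only, after t2; log-odds of loss rising by 1 per NPS point at t2. In a simulation of 400,000 women per setting, the completers' mean in that arm was too low by:

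| Correlation | t2 | t3 |
|---|---|---|
| 0.3 | 0.34 | 0.10 |
| 0.5 | 0.34 | 0.17 |
| 0.7 | 0.34 | 0.24 |

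With 10% lost, the figures are 0.18 at t2 and 0.05 to 0.13 at t3. Loss here depends only on an observed value, so the data are missing at random. A correctly specified likelihood-based model using all observed values does not carry this bias; the complete-case analysis does.

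**7. The two sections side by side.** Statistical analysis claims intention to treat. Materials and methods excludes women for stopping the intervention, which can happen only after allocation, and for failing the walk test or becoming unstable, which can. Taken literally, both cannot be followed.

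**The case against.** The strongest reply is that this is a condensed article. The sentence may be a loose way of saying that all randomised women will be kept, with the filling-in method set out in a full protocol or SAP that is not shown. That stands in part. If values are imputed before the ANOVA, the analysis is not complete-case, so the conclusion must be conditional on the text as written. It does not rescue the sentence, which gives intention to treat as the handling of missing data and is wrong on that whatever another document adds.

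A reader might also infer more than the documents support:

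- *That the trial will be short of women or power.* About 70 completers is what the plan was sized for, and step 5 shows adequate power.
- *That precision at t2 falls by 12%.* That needs every loss to fall at t3. Women lost before t2 have no t2 value to waste.
- *That early discharge drives the losses.* The protocol does not mention it. The documented routes are the listed exclusions.
- *That a bias of a given size is to be expected.* Step 6 is a scenario, not a forecast.

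Finally, a mixed model is not the only cure. That is correct: multiple imputation before the planned ANOVA would also do.

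**Conclusion.** The point holds in conditional form. The missing-data sentence is wrong as it stands, and following the section as written, with nothing imputed, gives a complete-case analysis called intention to treat. The exclusions in Materials and methods contradict that label independently of the model.

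At the plan's 20% allowance about 18 of 88 randomised women would be left out. The cost in precision at t2 is 0 to about 12%. The more serious risk is bias, of the order of a few tenths of an NPS point under the assumed one-arm scenario, against a design difference of 2 points. These sizes rest on the allowance being realised and, for bias, on an assumed loss mechanism. The correction should be made, but nothing here shows that the trial cannot answer its question.

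**What to change.** 1. In Statistical analysis, replace the repeated-measures ANOVA, Mauchly and Greenhouse-Geisser text, together with the missing-data sentence, by wording such as: *All randomised women are kept in their allocated arm. The primary analysis is a likelihood-based linear mixed model (SPSS MIXED) using every observed assessment; it is valid if data are missing at random.* Then choose one form and state it:
   - t1, t2 and t3 all as outcomes; or
   - t2 and t3 as outcomes with t1 as covariate, plus a reported count of women with no post-baseline value, since they contribute nothing to that model.

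   Multiple imputation before the planned ANOVA is an acceptable alternative. In that case the ANOVA text stays and the imputation is named.
2. Add one sensitivity analysis for data not missing at random: add a pain penalty to imputed missing values, over a range and in arms stated in advance (for example 1 and 2 NPS points; these sizes are illustrative).
3. Reconcile the exclusions in Materials and methods with intention to treat, so that events after allocation do not remove women from the analysis. This concerns the analysis set only, not clinical management.

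The cost is some rewording and one extra analysis run. No new data are needed, and the named software has the procedure.

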This study will have three investigators: the first will be responsible for randomization, the second for assessments, and the third for delivering the intervention. This will be a blinded study because the second investigator and the patients will be unaware of the allocation and intervention.

This protocol was approved by the research ethics committee of the Federal University of Rio Grande do Norte (Brazil) (CAAE: 53263721.5.0000.5537) and submitted to the Brazilian Registry of Clinical Trials (RBR-9pjd2n3). The autonomy and anonymity of patients will be respected, and personal data privacy will be ensured following resolution no. 510/16 of the National Health Council and the Declaration of Helsinki. Before entering the study, all patients will sign the informed consent form for written. The flow chart of study protocol is described in Fig 1 (Fig 1).

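### The outcome spreadsheets are assigned to the investigator who randomises, who is not among those the plan lists as blinded

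*Protocol article*

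**What the plan says.** Materials and methods divides the work among three investigators: "the first will be responsible for randomization, the second for assessments, and the third for delivering the intervention". It then says who is masked: "This will be a blinded study because the second investigator and the patients will be unaware of the allocation and intervention". The first investigator is not included in that statement.

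The same section describes the allocation: "The sample will be randomized (www.randomization.com) in four groups", followed by "The groups will be coded, and allocation will be done in sealed and opaque envelopes, numbered consecutively". It does not name who holds the key to the codes.

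The last paragraph of Statistical analysis, on data management and quality control, says that "the investigator responsible for randomization will be responsible for organization the collected patients information in spreadsheets". The only safeguard given there is that this person will "ensure confidentiality without personal identification of the research participants".

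The exclusion criteria in Materials and methods include events that can occur after entry: stopping the intervention, not performing the 2-minute walk test, and "presence of clinical or obstetric instability during the assessment period".

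**The concern.** The division of roles keeps the person who measures outcomes from knowing the arm. The data-management sentence then passes the measured outcomes to the one investigator whose job is the allocation. If that person can see the arm and the pain score side by side while the file is assembled, small decisions may be made with knowledge of the arm: how an unclear entry is read, which discrepancies are queried, and whether a participant with a possible exclusion event stays in. The primary outcome is pain, compared across four groups of 22, so a few such decisions in one group could matter.

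The article states this assignment outright. It is not a detail left to a fuller document.

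**Working it through.** No figure in the plan bears on this point, so the check sets the stated roles and safeguards side by side.

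**Step 1: who does what, and who is masked.**

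- First investigator: randomisation (Materials and methods) and the data spreadsheets (Statistical analysis). Not listed as masked.
- Second investigator: assessments. Listed as masked.
- Third investigator: delivers the intervention. Not listed as masked, and cannot be.
- Patients: listed as masked.

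The data task therefore falls to someone outside the masked roles, although one of the three investigators is masked.

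**Step 2: does any stated safeguard hide the arm from the first investigator?**

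- Sealed, opaque, numbered envelopes conceal the next allocation at enrolment. They do nothing for a data file assembled afterwards.
- Coded groups mask a reader who lacks the key. Whoever is responsible for randomisation can be presumed to have the key or to be able to reconstruct it. This is an inference, because the holder is not named.
- Removing personal identifiers protects privacy. It does not conceal the arm.

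None of the three closes the gap.

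**Step 3: which decisions could be affected?**

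- Measurement: not affected. Scores are taken by the masked assessor.
- Entry, transcription and queries: exposed, if organising the data includes them, as it ordinarily would.
- Post-entry exclusions: a discontinued intervention and a failed walk test are observable events with little room for interpretation. Instability requires judgement. The article does not say who applies these exclusions.
- Analysis set: Statistical analysis names intention to treat as the approach to missing data, while Materials and methods lists the post-entry events as exclusions. The article leaves open who stays in, so membership may still have to be decided when the file is assembled.

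**Step 4: effect on the design figures.** None. The plan's numbers are 17 per group with 20% losses: 17/(1 − 0.20) = 21.25, rounded up to 22, and 4 × 22 = 88. Moving a data task between investigators changes neither these nor the alpha or power.

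**The case against.** The strongest reply is that the sentence grants only the organising of spreadsheets and the keeping of confidentiality. It gives this person no power to resolve queries, drop participants or define the analysis set. Instability and a failed walk test arise at the bedside during assessment, and the article never claims a blinded data manager or analyst, so it does not contradict itself. Database lock, arm-free files and neutral group labels are commonly left to a full protocol or data-management plan. Giving the file to the assessor also has a price: that person would handle their own earlier records, and the separation of collecting data from organising them would be lost.

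Much of this stands. The wider powers are inferred, there is no internal contradiction, and the absence of lock procedures is not held against the article. What remains is the role assignment, which is stated text and which the listed safeguards do not offset.

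Three stronger readings are tempting and are not supported:

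- A reader might infer that blinded assessment is lost. It is not. The masked measurement stands, and only later handling is exposed.
- A reader might infer that the choice between the two walk attempts is open to influence. The Functional capacity (2MWT) section settles it by rule, since the longer distance is recorded, so only its transcription is exposed.
- A reader might try to size the bias by removing the highest pain scores from one arm. High pain is not an exclusion criterion, so that would model deliberate selection outside the protocol and would not measure this weakness.

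**Conclusion.** The point holds as a weak design choice of low to moderate severity. The investigator assigned the outcome spreadsheets is not among those listed as blinded, and nothing stated hides the arm from that person. The exposure covers entry, transcription, queries and any role in applying exclusions, chiefly instability. The size of any bias is unknown, and the document gives no basis for a figure.

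The conclusion assumes that responsibility for randomisation brings the ability to link records to arms, that organising the data includes entering or checking them, and that the assessor is masked as stated. If a fuller document shows that the allocation key is held by someone else and is out of this investigator's reach, the concern largely falls away.

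**What to change.** Change the data-management sentence in Statistical analysis so that:

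- the blinded second investigator enters and organises the outcome data under study ID, in a file with no arm column;
- the randomising investigator keeps only the allocation list and has no access to outcome data until the file is locked;
- queries and analysis-set membership, including any exclusion for instability, are settled and recorded before the allocation list is merged.

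The cost is a little more work for the assessor, who would handle their own earlier records. To limit this, enter each participant's data only after the third assessment, so that earlier scores are not revisited between visits, and check the entries against the source forms. The change needs no additional staff or participants and leaves sample size and alpha as they are. The article describes recruitment as under way, but the separation can still be applied at any time before allocation and outcomes are merged. If some records have already been organised under the present rule, the date of the change should be reported.
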